### Participants

Gaps in VLM will be identified in HIV-positive patients aged ≥ 16 years who started ART in the previous 15–18 months in any of the 10 trial clinics through a retrospective review of their clinical charts.

The intervention will be evaluated in all patients aged ≥ 16 years who have been on ART for ≥ 12 months during the study’s baseline time period and attend any of the 10 trial clinics during a three-month recruitment period. No exclusion criteria will apply as there will be no individual enrolment to the trial, rather routine clinical data will be used for the evaluation of the outcomes.

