### Description of the intervention

#### Quality improvement package

We will adapt the VL champion model described by Sunpath et al. [17]. This model identifies a VL champion in each clinic who dedicates 10 h per week to the role. The VL champion ensures those with high VL are appropriately managed with repeat VL tests including referral to a doctor for second line ART switch if required.

The prototype QIP will be adapted based on the identified clinical and process impediments in VLM from the gap analysis. All nursing/assistant staff in the intervention clinics will be trained on the QIP using the model by Sunpath et al. as described above [17]. Each intervention clinic will identify two key nurses who would act as VL champions. Their role will include tracing and recalling patients who need further assessments of their VL or switch to second-line regimen.

Training will be provided in the use of enhanced TIER.Net technology that will be developed as part of the trial and how to access reports on the dashboard system.

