#### Augmentation of TIER.Net with a dashboard system

TIER.Net is an electronic database with varying levels of sophistication in both functionality and reports. It ranges from an off-line version of the electronic register to hybrid that is predominantly offline, with synchronisation centrally when bandwidth allows to a networked electronic version of the paper register [9]. The offline version of TIER.Net is in operation in the public ART programmes in which this study will be embedded.

As part of the proposed intervention, VL results will be imported into TIER.Net daily from the National Health Laboratory Service (NHLS) which will be linked to patients in TIER.Net based on multiple exclusive and linked deterministic rules using a combination of variables such as name, surname, sex, date of birth, date of visit, NHLS lab number, facility and folder number. The information contained in TIER.Net will be used to develop a dashboard which will display the following information:The proportion due VL tests as per South African ART guidelines.The proportion with high VLs (VL ≥ 50 copies/mL).The proportion lost to follow-up.Those with confirmed virological failure (repeat VL ≥ 1000 copies/mL after a first VL 1000 copies/mL measured ≥ 3 months apart).

A dashboard has the advantage of displaying a quick visual state of affairs and how this evolves with time. This will incorporate a text messaging functionality that can be used by healthcare workers/viral load champion to communicate with patients.

It is envisaged that these interventions will result in prompt identification of patients who require VLM, and improve clinical management of virological failure thereby improving the quality and efficiency of service delivery.

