### Standard of care

Viral load results are manually captured on to the TIER.Net system with filing of the paper results in patients’ clinical notes for nurses’ review during routine appointments. This is used to produce a monthly enrolment and quarterly cohort reports for the central monitoring of the ART programme.

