#### Evaluation of the intervention

The effectiveness of the intervention will be evaluated in HIV-positive individuals aged ≥ 16 years attending the trial clinics who have been on ART for at least 12 months at baseline (the evaluation cohort).

AHRI has a clinical research assistant stationed in each of the ten clinics who registers every patient attending the clinic, irrespective of their reason for attendance or HIV status. A database, known as ClinicLink, was developed in-house at AHRI for the registration of clinic visits and reasons for attendance. ClinicLink will be used to identify patients attending the clinic who meet the criteria for inclusion in the evaluation cohort. Based on current clinic attendance, we will need about three months to meet the target sample size of an average of 150 patients per clinic. These individuals will form the basis for the main analyses. In secondary analyses, all patients meeting these criteria who attend one of the trial clinics during the three-month recruitment phase will be included in the evaluation cohort, even if the sample size is exceeded since the target sample size is considered a minimum. If the target sample size is not met within 3 months, we will extend the recruitment phase for another month as necessary.

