### Trial procedures and timelines

We will pilot the interventions over 3 months to address any issues raised and deliver further training to the nurses or adaptation of the technology if required (Fig. 2). Patients attending for their routine clinic visits over a three month period, which we estimate is the time required for at least 150 participants to pass through each clinic, will be included in the evaluation cohort and followed up for a period of 14 months to allow a 2 month window for appointment reschedules etc.

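### The evaluation cohort is defined by clinic attendance in a window described after the pilot, and nothing in the readable text closes entry before allocation or go-live, so the intervention can change who is analysed

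*Protocol article*

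**What the plan says.** **Who enters the cohort.** Participants admits patients aged 16 or over, on ART for at least 12 months in an undated baseline period, who "attend any of the 10 trial clinics during a three-month recruitment period". There are no exclusion criteria and no individual enrolment. Under Recruitment (Evaluation of the intervention), "ClinicLink will be used to identify patients attending the clinic who meet the criteria for inclusion in the evaluation cohort". ClinicLink registers every attender whatever the reason for the visit. Of the average of 150 per clinic obtained this way, the article says "These individuals will form the basis for the main analyses".

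**When.** Trial procedures and timelines opens with "We will pilot the interventions over 3 months to address any issues raised and deliver further training to the nurses". It then turns to cohort entry: "Patients attending for their routine clinic visits over a three month period". No calendar dates are given for allocation, pilot, go-live or baseline, and the study timeline figure is not available in the text.

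**What the intervention does to attendance.** On the champions, Quality improvement package says: "Their role will include tracing and recalling patients who need further assessments of their VL or switch to second-line regimen". On the dashboard, Augmentation of TIER.Net says: "This will incorporate a text messaging functionality that can be used by healthcare workers/viral load champion to communicate with patients". Standard of care, by contrast, describes data handling for review at routine appointments: "Viral load results are manually captured on to the TIER.Net system with filing of the paper results in patients’ clinical notes".

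**The concern.** Clinics are randomised, but the patients analysed are picked by a behaviour, attendance, that the intervention is meant to influence. If the attendance window is open while champions are recalling and texting, an intervention clinic's cohort may include patients who would not have come in during those three months under current care. A control clinic's cohort would have no counterpart to them. The arms could then differ in the kind of patient they contain as well as in the care given, and the primary comparison of clinic proportions would mix the two.

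Enrolling more patients does not reduce this kind of bias. It is also difficult to correct at analysis, because the control patients who would have been recalled are not identified.

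**Working it through.** **1. The plan's own figure.** Inputs from Sample size justification: 5 clinics per arm, m = 150, k = 0.20, 50% v 77%, stated power 80%. Two-sided 5% is assumed, to match the planned 95% CI. The standard unmatched cluster-trial formula, with one cluster per arm added, gives:

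- variance term = p0(1−p0)/m + p1(1−p1)/m + k²(p0² + p1²) = 0.25/150 + 0.1771/150 + 0.04 × (0.25 + 0.5929) = 0.03656
- z = √[(5−1) × 0.27² / 0.03656] = 2.824
- power = Φ(2.824 − 1.960) = 80.6%

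The stated 80% reproduces. The sample size is not in question; the issue is bias.

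**2. How few patients it takes.** Trial setting gives about 30,000 people on ART in 17 clinics. With equal clinic sizes (an assumption), that is 30,000/17 ≈ 1,765 per clinic. A cohort of 150 is about 8.5% of that. A 10–20% share of the cohort is 15–30 patients, or about 0.85–1.7% of the register.

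**3. Bias with no true effect.** Let f be the share of the intervention cohort present only because of recall or texting, and q their success proportion. Neither is in the document; both are assumptions. With 50% success in everyone else and in the control arm, intervention proportion = (1−f) × 0.50 + f × q, and RR = that / 0.50.

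| f | q | Intervention proportion | RR |
|---|---|---|---|
| 10% | 25% | 0.475 | 0.95 |
| 20% | 25% | 0.450 | 0.90 |
| 10% | 85% | 0.535 | 1.07 |
| 20% | 85% | 0.570 | 1.14 |
| 10% | 45% | 0.495 | 0.99 |
| 20% | 45% | 0.490 | 0.98 |
| 5% | 25% | 0.4875 | 0.975 |
| 5% | 85% | 0.5175 | 1.035 |

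For the rejection rate, take the planned test on log clinic proportions. There are 10 clinics less 4 stratum-by-arm cells, so 6 df; the variance per clinic is (1−p)/(150p) + 0.04. A nominal 5% test then rejects about 10% of the time at RR 0.90 and 13% at RR 1.14. In the two rows with f = 5% it rejects about 5.3–5.5%.

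**4. Effect on the planned contrast.** With 77% in non-recalled intervention patients and q = 45%, the intervention proportion is 0.9 × 0.77 + 0.1 × 0.45 = 0.738 at f = 10%, and 0.8 × 0.77 + 0.2 × 0.45 = 0.706 at f = 20%. The RR moves from 1.54 to 1.48 and 1.41. Power of the same 6-df test moves from 77% to 68% and 58%. Its 77% differs from the 80.6% above because it is a t-test on the log scale.

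**5. Does any section prevent this?**

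- *Universal registration (Recruitment)* removes staff discretion over who is enrolled. It does not make attendance independent of arm.
- *The word routine in Trial procedures and timelines* could be meant to leave out prompted visits. Participants and Recruitment apply no such filter, although ClinicLink does record reasons for attendance.
- *The adjusted analysis (Statistical analysis)* is optional and can only balance what was measured.

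**The case against.** The strongest reply is that the timing is inferred. It rests on the order of two sentences, and the timeline figure that could settle it is not shown. If the window closed before any intervention activity, the problem would disappear. That stands as a limit on the claim, but the readable text does not say so, and nothing else in it fixes the order.

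Several stronger readings are tempting and the article does not support them:

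- A reader might infer that the dashboard lists overdue and lost patients for recall. It is described as showing the proportions due a VL and lost to follow-up; only the confirmed-failure item is worded as naming patients. No section gives champions the task of tracing people lost to care, so enrichment with lapsed patients is not established.
- A reader might infer that control clinics do no recall. Standard of care is silent on it, and Background describes national guidance to retest high VLs, which is not limited to intervention clinics.
- A reader might infer that baseline adjustment is useless because baseline is post-intervention. TIER.Net holds dated VL results, so results from before allocation could be used where they exist. The extraction date is not given.
- A reader might infer that randomisation protects nothing. Clinic allocation remains stratified, restricted and concealed; what is exposed is the make-up of the patient cohort.

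It is also fair that the assumed shares drive the size, and that at some values the bias is negligible. None of this removes the gap. An analysis plan cannot undo how a cohort was assembled.

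**Conclusion.** The concern holds in this form: as the readable text stands, entry to the main-analysis cohort depends on attendance in a window described after the pilot, with no stated closure before allocation or go-live. The intervention includes recall and texting that the described current care does not. Following the plan as written therefore allows post-randomisation identification bias in the primary comparison.

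Direction and size are unknown. Recalled patients with high VL would pull the effect down; recalled patients who are then tested and suppressed could push it up. Under assumed shares of 10–20% and success of 25% or 85%, the RR under no true effect runs from about 0.90 to 1.14. With success of 45%, near that of the other patients, it is 0.98–0.99. The conclusion rests on the order of description in Trial procedures and timelines and on recall being more frequent in intervention clinics. It should be settled before the cohort is assembled, because repair afterwards is difficult.

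**What to change.** Define the primary cohort in all ten clinics from ClinicLink/TIER.Net records in one common calendar window that closes before allocation, or at the latest before the pilot starts. Keep the present criteria: aged 16 or over and on ART for at least 12 months. Then:

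- take all baseline variables, including VL, from results dated on or before the close of that window;
- analyse each patient in the clinic of registration, whether or not they later attend;
- start follow-up on one common date in all clinics;
- align Participants, Recruitment, Evaluation of the intervention impact, and Trial procedures and timelines with this rule;
- keep an attendance-based cohort, if wanted, as a sensitivity analysis.

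If the intended schedule already closes entry before any intervention activity, stating those dates in the same sections resolves most of the point.

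**Cost.** ClinicLink already covers all ten clinics, there is no individual enrolment, patient consent is waived, and the gap analysis already draws on a comparable sampling frame. The change is not entirely free. Time, including the pilot, may fall between the close of the window and the start of follow-up, so some listed patients will have left and will count as non-events in both arms. The per-participant 12-month and 14-month follow-up wording must also be revised to fit a common start date.

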### Allocation and blinding

The 10 clinics will be randomly allocated to the intervention (5 clinics) and control (5 clinics) arms. Randomisation will be stratified on clinic size, defined by the number of HIV-related visits per month (2 strata). Restricted randomisation will be used to ensure balance between study arms on the following important covariates: proportion of HIV patients who are male; proportion of HIV patients who are aged < 25 years. A computer programme will be used to prepare a list of all permissible randomised combinations; community leaders will be invited to make a random selection from the list at a public ceremony. The randomisation list will be prepared by an independent AHRI statistician and will be concealed until after randomisation. It will not be possible to blind the research staff and nurses to the intervention.

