### Trial design

#### Gap analysis

We will use a retrospective chart review of HIV positive patients in care at the 10 trial clinics to identify the health systems gaps in VLM. We will create sampling frame of individuals who are in care and started ART 15–18 months previously and select a random sample of 800 individuals from this frame. Clinical notes of these individuals will be reviewed to identify any gaps in the VLM process, and to identify predictors of missing viral loads. This information will be used to develop a QIP that includes training of staff on the current South African ART guidelines, the importance of VLM and both health system and individual risk factors for suboptimal VLM.

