#### Evaluation of the intervention

We estimate that during the 3 month recruitment phase, an average of 150 patients who have been on ART for ≥ 12 months will attend each clinic. Based on our previous work, we expect that around 50% of patients in the control arm will have a VL measurement and be virally suppressed at the end of follow-up. With 5 clinics per arm, assuming a coefficient of variation, k, of 0.20, and a sample size of 150 patients per clinic, we would have 80% power to detect an increase in the proportion of patients who have a VL measurement and are virally suppressed from 50% in the control arm to 77% in the intervention arm (Table 1).

**Table 1 Tab1:** Numbers needed to demonstrate an improvement in viral load monitoring, for different assumptions regarding clinic size and effect sizes

Number of clinics per arm	Number of patients per clinic^1^	Coefficient of variation (k)	% with VL suppressed in control	% with VL suppressed in intervention	Power (%)
5	100	0.20	45	67	71
5	100	0.20	45	70	80
5	100	0.20	50	74	71
5	100	0.20	50	77	80
5	100	0.20	55	80	70
5	100	0.20	55	84	80
5	150	0.20	45	66	70
5	150	0.20	45	69	80
5	150	0.20	50	73	70
5	150	0.20	50	77	80
5	150	0.20	55	80	70
5	150	0.20	55	84	80

^1^Harmonic mean to account for varying facility size

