#### Evaluation of the trial intervention

The effect of the intervention on the primary outcome (proportion of patients with VL suppression) will be estimated using a two-stage approach based on cluster (i.e. clinic)-level summaries [19]. The cluster-level approach, although less statistically efficient than methods based on individual level regression, is more robust when there are a relatively small number of clusters. Briefly, in the first stage, the proportion with VL suppression in each clinic will be calculated, and logarithmically transformed. In the second stage, the cluster-level summaries will be compared using a stratified t-test to test the null hypothesis of no intervention effect. Since equal numbers of clinics will be allocated to the 2 arms within each stratum, the unadjusted risk ratio (RR) for the intervention effect will be calculated as the ratio of geometric mean proportion with VL suppression for the 5 clusters in each arm. The 95% confidence interval (CI) will be calculated with the variance estimated from the residual mean square in a two-way analysis of variance of the log proportions on stratum and trial arm, incorporating a stratum by trial arm interaction. An adjusted analysis based on cluster-level summaries may also be done to account for covariate imbalance at baseline, using a similar two-stage process. All covariates will be pre-specified in a detailed analysis plan. In the first stage, an individual-level logistic regression will be done, including terms for stratum and all covariates except the intervention effect, and ignoring clustering. After fitting the regression model, a residual for each cluster will be calculated as the ratio of the observed to the predicted number of events. If the intervention has no effect, the residuals of the two arms should be similar on average. In contrast, if the intervention has an effect, we expect the residuals to differ systematically. Therefore, in the second stage, we will compare the residuals between the trial arms using the methods described above; residuals will be log transformed for the analysis. Analysis of the intervention effect on the secondary outcomes will be done using the same approach. A detailed statistical analysis plan will be prepared before to data analysis.

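### Randomisation is restricted on clinic sex and age mix but on no clinic-level baseline measure of the outcome, and baseline adjustment is only optional; with five clinics per arm this costs precision and credibility.

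*Protocol article*

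**What the plan says.** Under Allocation and blinding: "The 10 clinics will be randomly allocated to the intervention (5 clinics) and control (5 clinics) arms". Randomisation is stratified on clinic size in two strata, and the arrangements are further restricted on two covariates: "Restricted randomisation will be used to ensure balance between study arms on the following important covariates: proportion of HIV patients who are male", and then the proportion aged under 25 years. No measure of VL testing or suppression appears among the stratification or restriction variables.

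Under Statistical analysis, Evaluation of the trial intervention, the primary comparison is a stratified t-test on log clinic proportions. On baseline differences the text says: "An adjusted analysis based on cluster-level summaries may also be done to account for covariate imbalance at baseline". Covariates are left to a separate analysis plan.

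Sources for a pre-trial measure are described elsewhere. Data collection (Evaluation of the intervention impact) says TIER.Net holds VL results with dates. The Gap analysis section says: "We will use a retrospective chart review of HIV positive patients in care at the 10 trial clinics".

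**The concern.** The primary outcome is a composite of having a VL measured and being suppressed. The Discussion attributes poor monitoring largely to how clinics work: staff training and time, results not reaching the clinic, and manual capture. The intervention acts on those same processes. A clinic's own pre-trial VL performance measures them directly; its sex and age mix does so at best indirectly. Sex and age are also individual data that the first-stage regression could include.

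With ten clinics, one draw can leave the arms apart on baseline performance, and the demographic constraints need not prevent it. Readers may then question a positive or null result, and between-clinic variation that a baseline could explain stays in the error term. Restriction cannot be repaired after the draw, which leaves only the analysis, where adjustment is not firm.

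**Working it through.** **Inputs from the protocol.** Sample size justification: "With 5 clinics per arm, assuming a coefficient of variation, k, of 0.20, and a sample size of 150 patients per clinic"; and "we expect that around 50% of patients in the control arm will have a VL measurement and be virally suppressed at the end of follow-up". The target is 77% in the intervention arm with 80% power. Background: 34% of the formative cohort had a VL documented after 12 months on ART. The analysis section allocates equal numbers of clinics to each arm within strata, so strata must be even-sized.

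**Assumptions.** Two-sided alpha of 0.05 (inferred from the 95% interval); strata of 4 and 6 clinics; k applied to the baseline proportion as well as to the outcome.

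**1. The protocol's own power.** Standard unmatched cluster formula:
- V = p0(1−p0)/m + p1(1−p1)/m + k²(p0² + p1²) = 0.25/150 + 0.1771/150 + 0.04 × (0.25 + 0.5929) = 0.0366.
- z = √[(c−1)(p1−p0)²/V] − 1.96 = √(4 × 0.0729/0.0366) − 1.96 = 0.86, giving 80.6% power.

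The stated 80% reproduces, and all 12 rows of Table 1 agree within 2 points.

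**2. Chance imbalance in an unrestricted clinic baseline.** SD of the arm difference = k × p × √(2/5). At p = 0.50 and k = 0.20 this is 0.10 × 0.632 = 6.3 points, with a 95% range of ±12.4 points.

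| k | Baseline mean | SD of difference (points) | P(>5 points) | P(>10 points) |
|---|---|---|---|---|
| 0.20 | 50% | 6.3 | 43% | 11% |
| 0.15 | 50% | 4.7 | 29% | 3.5% |
| 0.30 | 50% | 9.5 | 60% | 29% |
| 0.20 | 34% | 4.3 | 24% | 2% |

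**3. Does restricting on sex and age help?** All C(4,2) × C(6,3) = 6 × 20 = 120 allocations were enumerated over simulated clinics, with both demographic arm differences held within 0.5 clinic-level SD (an assumed limit) and a 50% baseline mean. If each demographic correlates with baseline VL performance at r = 0, P(>5) is 43% and P(>10) 11%. At r = 0.3 they are 39% and 9%; at r = 0.5, 31% and 4%; at r = 0.7, 9% and about 0%. Only strong correlation removes the problem.

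**4. What reaches the outcome.** If baseline and outcome correlate at ρ across clinics, the carried-over difference has SD ρ × 6.3 points: 3.2 at ρ = 0.5 and 4.4 at ρ = 0.7. Removing that variation in the analysis reduces k to 0.20 × √(1−ρ²), which is 0.17 or 0.14. The formula in step 1 then gives about 90% or 97% power instead of 81%. Both ρ values are assumptions, and the power figures are approximate.

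**5. List length.** Under the limits in step 3, the two demographics leave a median of about 38 of 120 allocations; adding baseline VL within 3 points leaves about 14. With demographic limits of 0.75 SD of the arm difference and baseline VL within 5 points, the corresponding figures are 34 and about 20.

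**The case against.** The strongest defence is that nothing here is an error. Random allocation is unbiased, between-clinic variation is already in k = 0.20, and the cluster-level test and interval reflect it. This stands.

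A reader might infer more than the document supports:
- **That baseline VL performance is the strongest clinic-level predictor.** The document gives no clinic-level baseline data and no baseline–outcome correlation.
- **That a large imbalance is likely.** The median absolute difference is about 0.67 × 6.3 = 4.3 points against a 27-point target effect, and more than 10 points occurs in about one allocation in nine. The 50% is an expected end-of-follow-up value; the only pre-trial VL figure is 34% documented, where the chances are lower.
- **That imbalance would be inseparable from the intervention effect.** Baseline VL results are extracted for the evaluation cohort, so imbalance can be reported and adjusted for, and it carries over in full only if ρ = 1.
- **That swapping covariates leaves the list just as long.** A 5-point limit is 5/6.3 = 0.79 SD of the arm difference. Set beside a 0.75 SD demographic limit, a similar length follows by construction.

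The data sources are also imperfect. The chart review samples people who started ART 15–18 months earlier, whereas the evaluation cohort is anyone on ART for at least 12 months, and its listed outcomes concern documentation, not suppression. An even split of 800 would give 80 charts per clinic, with a standard error of √(0.25/80) = 5.6 points per clinic and 5.6 × √(2/5) = 3.5 points on the arm difference. The Discussion leaves open whether gaps in TIER.Net reflect missed tests or missed data entry. These points shape the remedy without removing the concern.

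The choice of adjustment covariates properly belongs to the analysis plan. The restriction covariates do not: this document fixes them, and it also makes adjustment optional.

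**Conclusion.** The concern holds as a design improvement. The restriction omits any clinic-level baseline measure of the outcome although pre-trial VL data exist, and the adjustment that could compensate is not firm. Moderate imbalance is a realistic chance event: about 43% for more than 5 points and 11% for more than 10, if the protocol's k applies to baseline and the baseline mean is near 50%. Across the inputs tabulated above, these chances run from 24% to 60% and from 2% to 29%. The consequence is lost precision and face validity; there is no bias, and neither the test nor the power calculation is invalidated. The benefit of acting depends on baseline VL performance predicting the outcome better than sex and age mix, which is reasonable but assumed.

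**What to change.** **Allocation and blinding, if clinics are not yet randomised.** Add as a restriction covariate each clinic's pre-randomisation proportion of patients on ART for at least 12 months who have a VL documented and suppressed. Take it from TIER.Net and check it against the chart review where that is available. Alternatively, swap it for one of the demographic covariates. Before the draw, enumerate the permissible allocations with the real clinic data and confirm that enough remain.

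**Statistical analysis, Evaluation of the trial intervention, whether or not clinics are randomised.** State that the adjusted cluster-level analysis will be done and will include baseline VL status. Define that status from records dated before randomisation and before the three-month intervention pilot. A value taken at cohort entry could already reflect the intervention if the pilot ran in intervention clinics, and adjusting for it could then remove part of the effect. Restriction alone does not shrink the residual variance used in the unadjusted test, so the gain in precision is realised mainly through this adjustment.

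**Cost.** One extra clinic-level variable from existing records. Used as a third constraint it shortens the list, to roughly 14–20 of 120 allocations under the assumed 4 + 6 strata and assumed tolerances.
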